**Methods:**

The study is a three-year, two-phase cluster-randomized trial in 18 communities in western Kenya. During Phase 1, six control communities were offered screening in health facilities; and six intervention communities were offered screening in community health campaigns. Screening was done with human-papillomavirus testing through self-collected specimens. Phase 1 ended and we are working in partnership with communities to further contextualize the implementation strategy for screening, and develop an enhanced linkage to treatment plan. This plan will be tested in an additional six communities in Phase 2 (enhanced intervention). We will compare the reach, efficacy, cost-effectiveness and adaptability of the implementation strategies.

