In Phase 1 of this study, we compared two implementation strategies that incorporated these four evidence-based elements of screening. Based on our preliminary data, we found that reaching and attending a health facility for preventive care was a significant barrier to screening for many women. Therefore, the main objective was to compare a model offering screening in brief, high throughput community health campaigns to that of a standard of care in which screening was offered in local health facilities using the metrics defined in the modified RE-AIM framework.

In Fig. 1, we present an overall schema of the cluster-randomized trial. In Phase 1, six communities were randomized to the intervention: HPV screening carried out in **community health campaigns**. The remaining six were comparison communities: HPV testing offered in **government health facilities**. HPV-test positive women in all communities were referred to the County hospital for immediate treatment, which is considered standard linkage to treatment.

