**Fig. 1 Fig1:**
[figure not shown]
Two-phase cluster-randomized trial design

Development of an enhanced strategy for linkage to treatment: After Phase 1, we have an “inter-phase intervention development” period in which we are evaluating the results from the trial. The outcomes from the qualitative and quantitative measures will be used to refine the screening intervention using context-specific details and develop an enhanced strategy for linkage to treatment. Although we have identified factors that enable and inhibit women’s access to treatment, we chose to wait until after Phase 1 for the development of the enhanced strategy for linkage to treatment in order to truly work in partnership with the community. The delayed development of the linkage to treatment strategy has allowed us obtain a baseline measure of the efficacy of standard referrals and identify factors that would influence women’s access to care in this setting.

After developing the strategy for enhanced linkage, we will pilot and then test the linkage to treatment strategy as part of an “enhanced intervention” in the six communities that served as controls in Phase 1. Using these communities for the enhanced intervention increases the efficiency of the study in two ways: i. we will have done community enumeration and engagement, and ii. we will compare linkage to treatment outcomes from these “enhanced intervention” communities to the intervention communities from Phase 1.

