**Provider and key stakeholder focus groups:** Clinicians and community health workers (“providers”) within the community health campaigns and health facilities participated in focus group discussions to provide baseline data about perceived barriers and strategies to facilitate HPV screening uptake during the planning and implementation adaptation period of the study. Although we sought key stakeholder input throughout the development of the implementation strategies, we held three focus group discussions with key stakeholders in the intervention and control communities for Phase 1 (community chiefs, leaders of women’s groups, reproductive health coordinator, medical superintendent and Charge Nurse of Migori District Hospital). The goals of these focus groups were to obtain a group perspective on the intervention as planned for their communities, any anticipated challenges and strategies to optimize the screening strategy in both arms. Focus group discussions were analyzed using the theoretical domains framework, which mapped behaviors to intervention strategies, using evidence-based principles of behavior change [42].
**Training and finalization of the screening protocol.** We used educational modules piloted in western Kenya to provide standardized training in cervical cancer counseling and HPV-self testing to community health workers and clinicians [43]. The community health workers received training in community outreach messaging, delivery of the educational module in the community health campaign setting, and teaching women how to perform self-collection of HPV specimens. In addition to the general training, clinicians had undergone Ministry of Health-supported training to learn the cervical cancer screening protocol, including follow-up and pre-treatment exams. Two nurses who had undergone cryotherapy training were identified and supervised for ten cryotherapies at the County Hospital prior to study initiation.

#### Cluster randomized trial: Phase 1

After community enumeration, training and protocol finalization, we launched the cluster-randomized trial in the six control and six intervention communities in Migori County. (Figure 2) Phase 1 of the trial, consisting of the activities listed below, took place over the course of 1 year.

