#### Primary and secondary endpoints

To determine the **reach** of cervical cancer screening using HPV-testing in community health campaigns compared to clinics, we are using the following metrics: i) the absolute number of women who completed screening in each arm and ii) the proportion of women in each arm who completed screening. The total number of women in each arm is the number of women 25–65 in each community as determined by census data. Secondary outcomes will include iii) the proportion of women who accept screening among women offered at each site and iv) the proportion of women in the clinic-based arm who request clinician-collected specimens.

To determine the **efficacy** of a community-developed strategy to increase treatment access, we will compare the efficacy of the community-based HPV testing with standard versus enhanced linkage to treatment using the following metrics: i) the number of women who receive treatment after screening HPV + in the intervention (Phase 1) compared to the enhanced intervention (Phase 2) and ii) the proportion of HPV-positive women in each arm who complete treatment. Secondary outcomes that address quality of care concerns for the models will include iii) the proportion of women who receive the correct treatment (per Ministry of Health protocol) during a single treatment visit and iv) the average time between HPV testing and access of treatment by arm.

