#### Statistical analysis

*Preliminary Analysis:* For each outcome, we will produce descriptive statistics (frequencies, proportions, etc.) overall, across clusters of interest (community, clinic, provider, etc.), and over time. We will also graph these data to identify visual trends.
*Primary and Secondary Analysis:* Although this is a community-level intervention, the main outcomes will be analyzed at the individual level. We will compare the number and proportion of women who screen for HPV (reach) and who get treated for a positive HPV test (efficacy) in communities assigned to community vs. clinic-based testing using generalized estimating equations to account for the correlation among observations within communities. Efficacy: We will employ a log link and Poisson distribution with an offset term to represent the size of each community.
*Power calculations:* We anticipate being able to observe a 30% difference in overall screening uptake between the control and intervention arms, a conservative estimate relative to previous cluster randomized trials. The power calculations assume an alpha of 0.05, a beta of 0.20, and an intracluster correlation coefficient of 0.072 for screening and 0.11 for treatment, based on calculations from a cluster-randomized trial of HPV efficacy [5].

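### With six communities per arm, the stated GEE analysis has a type I error of about 10% if run with the usual uncorrected robust variance and normal reference; a small-sample method should be fixed.

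*Protocol article*

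**What the plan says.** The Statistical analysis section of the protocol article states that, although the intervention is at community level, the main outcomes are analysed on individuals. Numbers and proportions screened (reach) and treated (efficacy) are compared "in communities assigned to community vs. clinic-based testing", "using generalized estimating equations to account for the correlation among observations within communities". Under the Efficacy label it adds: "We will employ a log link and Poisson distribution with an offset term to represent the size of each community". The power statement assumes an alpha of 0.05, a beta of 0.20, and intracluster correlations of 0.072 for screening and 0.11 for treatment.

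The number of clusters is fixed elsewhere. Study design and setting: "In Phase 1, six communities were randomized to the intervention", with the remaining six as comparison. The Phase 1 section: "we launched the cluster-randomized trial in the six control and six intervention communities in Migori County". The enhanced strategy is then tested "in the six communities that served as controls in Phase 1". The abstract instead describes a "two-phase cluster-randomized trial in 18 communities in western Kenya", but it too gives six communities per compared group.

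The article does not say whether standard errors are robust or model-based, which reference distribution applies, or whether a small-sample adjustment is used.

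**The concern.** The robust (sandwich) variance that usually accompanies GEE is justified when the number of clusters is large. With few clusters it is biased downward, because residuals are taken around arm means fitted to the same handful of communities. A normal reference then ignores how imprecisely that variance is estimated. Both faults act in the same direction: p-values too small and intervals too narrow.

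The number of women does not help. About 1000 eligible women per community is ample within a community, but the arm comparison rests on 12 community-level units. By choosing individual-level GEE, the plan also sets aside the community-level analysis that would be close to nominal at this size without any adjustment. At stake is whether the 0.05 level in the power statement is what the analysis delivers.

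**Working it through.** **Inputs from the article.** Six communities per arm; about 1000 eligible women per community; expected uptake 510/1000 = 51% and 210/1000 = 21%; intracluster correlation (ICC) 0.072 (screening) and 0.11 (treatment); alpha 0.05.

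**Assumptions.** Two-sided test (not stated); beta-binomial variation between communities; coefficient of variation (CV) of community size 0 to 0.5; 50 to 150 HPV-positive women per community and treatment rates of 30 to 70%, neither of which the article gives.

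**The plan's own figures.** The totals reproduce: 6 × 510 = 3060 and 6 × 210 = 1260. The 80% power does not:
- Design effect = 1 + 999 × 0.072 = 72.9, so effective n per arm = 6000/72.9 = 82.3.
- For 51% v 21%, SE = sqrt[(0.51 × 0.49 + 0.21 × 0.79)/82.3] = 0.0711, and 0.30/0.0711 = 4.22.
- Power is about 99% with a normal reference (4.22 − 1.96 = 2.26) and about 97% with a noncentral t on 10 df.
- If the 30% is relative, normal-reference power is about 15% (27.3% v 21%) or 33% (51% v 39.2%).

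**Type I error, closed form.** With six equal-sized communities per arm, the sandwich divides each arm's sum of squares by 6 where the unbiased estimate divides by 5. Its SE is therefore sqrt(10/12) = 0.913 of the unbiased one. Rejecting when |z| > 1.96 amounts to rejecting when |t10| > 1.96 × 0.913 = 1.789, and P(|t10| > 1.789) = 0.104. The correct multiplier is 2.228, so intervals have 1.789/2.228 = 0.80 of the width they should have. Changing only the reference to t10 is not enough: 2.228 × 0.913 = 2.034, and P(|t10| > 2.034) = 0.069.

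**Simulation under no effect** (100,000 replicates per scenario, independence working correlation):

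| Method | Type I error |
|---|---|
| Robust, normal: screening, ICC 0.072 | 0.100–0.134 |
| Robust, normal: treatment, ICC 0.11 | 0.091–0.130 |
| Robust, t10: both outcomes | 0.059–0.094 |
| Kauermann-Carroll, t10: both outcomes | 0.041–0.064 |
| Mancl-DeRouen, t10: both outcomes | 0.028–0.042 |

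The log and logit links, compared for screening, differ little. Unequal community sizes make the inflation worse: for screening at 51% with the log link it rises from 0.0995 at CV 0 to 0.128 at CV 0.5. A separate set of 40,000-replicate runs gave 0.049–0.052 for a cluster-level t-test.

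**Exchangeable Poisson GEE** (1,000 to 1,500 replicates): robust SEs with a normal reference gave 0.094–0.119. Model-based SEs gave 0.061 (ICC 0.072) and 0.049 (ICC 0.11), so no doubling. Those two results need care. A Poisson variance p exceeds the binary variance p(1 − p) by 1/(1 − p), which is 1.56 at the 36% simulated for screening and 1.67 at the 40% simulated for treatment. An overstated variance works against the small-sample bias, so near-nominal error here does not show that the model-based SE is a valid small-sample method.

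**The case against.** The strongest reply is that a condensed article need not name the sandwich correction or reference distribution; those belong in the full protocol or SAP, which are not shown. GEE is compatible with every remedy proposed here. This largely stands. A reader might infer from the silence that no correction will be used and that the error rate is doubled as a fact of the plan. The documents do not support that: inflation requires the robust estimator, left uncorrected, with a normal reference, and none of the three is stated. What survives is that the article does fix individual-level GEE with 12 communities, and that this method in its usual form does not hold the stated alpha.

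A second reply is that model-based standard errors did not inflate the error. That also stands, and it limits the point to robust inference, with the caveat above about the variance model.

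A reader might also infer that both primary comparisons are affected. The GEE sentence covers both outcomes, but only for community versus clinic-based testing. Primary and secondary endpoints defines efficacy as the Phase 1 intervention against the Phase 2 enhanced intervention, and no model is expressly assigned to that contrast. The conflict between 18 and 12 communities does not alter six per compared group, though a joint model over 18 would not have 10 degrees of freedom.

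Finally, the expected reach effect is so large that the correction would seldom change that conclusion. This is fair for the test at 51% v 21%; it does not rescue interval width. Nor does it extend to treatment, for which the power statement gives no effect size.

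**Conclusion.** The point holds in conditional form. For reach and treatment in community versus clinic-based testing with six communities per arm, an uncorrected robust Wald test against the normal distribution has a two-sided type I error of about 10% (0.104 in closed form; 9 to 13% in simulation) instead of 5%. The closed form does not involve the ICC, and the simulated ranges at 0.072 and 0.11 are similar. The range rests on a two-sided test, beta-binomial clustering, the assumed spread of community sizes, and the assumed numbers and treatment rates of HPV-positive women. If the full protocol or SAP already specifies a small-sample method, confirming that closes the point. The figure carries over to the Phase 1 intervention versus Phase 2 enhanced contrast only if GEE is used there with the same 6 v 6 structure.

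**What to change.** State that GEE inference for the 12-community comparison uses a bias-corrected sandwich variance, for example Kauermann-Carroll, with a t reference on 12 − 2 = 10 degrees of freedom. Support it with a cluster-level t-test on community proportions or, for the randomised Phase 1 contrast only, a permutation test over the C(12,6) = 924 allocations. State which model applies to the Phase 1 intervention versus Phase 2 enhanced contrast and, if it is GEE, apply the same correction with degrees of freedom matched to the communities in that model. The cost is a sentence of analysis text, a software option and slightly wider intervals; power for 51% v 21% remains about 97%.

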#### Implementation framework

The study design, and outcome measures are centered in the essential implementation metrics as defined by the RE-AIM framework, which modified to the context of our study (Table 1) [17]. Outcomes will be evaluated through quantitative, qualitative and process measures. This design will allow us to test the following hypotheses:Community-based cervical cancer screening will reach a larger portion of eligible women and be more acceptable to patients and providers than clinic-based testing. (REACH)A community-driven intervention will improve linkage to treatment among women who need treatment after an HPV-positive screening test compared to standard referral. (EFFICACY)We will identify modifiable patient and health system challenges that can be addressed to make health campaign based HPV testing and enhanced linkage to treatment succeed and be sustainable. (ADOPTION & MAINTENANCE)Community-based cervical cancer screening with enhanced linkage to treatment will have a greater population-level health impact as measured in women reached with screening and any necessary treatment, and favorable cost-effectiveness profile compared to clinic-based strategies and standard referral for treatment. (IMPLEMENTATION)

**Table 1 Tab1:** A modified RE-AIM framework to evaluate community health campaign-based cervical cancer screening compared to health-facility based screening

	Dimension Goal	Implementation Question	Hypothesis
Reach	Who is intended to benefit?	How do we reach reproductive-aged women in rural kenya?	A screening strategy offered through community health campaigns in a central location will reach a large proportion of reproductive-aged women.
	How do we reach them?		
Effectiveness	Is the program effective?	Are women getting screened for cervical cancer with HPV?	A community-based strategy allowing for self-testing will be highly acceptable.
	How do we ensure effectiveness?	Are HPV + women successfully linking to treatment?	Innovative, patient and provider-designed strategies will increase the number of women linking to care.
Adoption and Maintenance	How can strategy be maintained after initial implementation and adopted in similar communities?	What are the patient, provider and delivery system processes necessary to ensure consistent service provision?	A screening protocol with a simple, patient-performed test offered as part of a health fair will minimize the costs to the health care system to introduce screening.

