#### Sample size

Using estimates from the 2009 Kenya census [45] with projected population growth for 2015 and results from recent community-wide census enumeration carried out by a cluster randomized trial in an adjacent district [46], we have estimated the total available population of women to be approximately 1000 per community of 5000. The estimates for attendance at community health campaigns (60% or 600 women) and clinics (30% or 300 women) and screening uptake were based on our formative work, community health campaign attendance in adjacent districts, and prior studies of self-collected HPV testing [27, 28, 47]. Our assumptions were that (1) attendance would be higher at community health campaigns and (2) screening uptake would be higher among women attending community health campaigns because most women attend based on outreach messaging around cervical cancer. These assumptions suggested a study population of 510 women per community accessing testing through community health campaigns and 210 accessing screening through clinics. For Phase 1, the total number of women accessing screening in the six communities randomized to community health campaigns would be 3060 and 1260 in communities randomized to clinic-based testing. We used these conservative estimates for sample size calculations (see below), but allocated resources for up to 4500 women in the community-testing arm and 2000 women in the clinic-based screening arm to ensure continuity of study activities. We also enrolled all providers and targeted key ministry of health stakeholders for quantitative and qualitative assessments of barriers and facilitators to care. A representative subset of this group were invited to participate in meetings to develop the enhanced linkage intervention.

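### The community-size offset in the efficacy model suits the number of women treated, but it does not estimate the proportion of HPV-positive women who complete treatment

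*Protocol article*

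**What the plan says.** The Statistical analysis section of the protocol article plans generalized estimating equations (GEE) for the number and the proportion of women, both for reach and for efficacy. It describes efficacy as women "who get treated for a positive HPV test (efficacy) in communities assigned to community vs. clinic-based testing". It says that the main outcomes are analysed at the individual level. Then, under the label Efficacy, it states: "We will employ a log link and Poisson distribution with an offset term to represent the size of each community". This is the only link, distribution or denominator that the section gives.

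Primary and secondary endpoints gives two main efficacy metrics. The first is a count: "the number of women who receive treatment after screening HPV + in the intervention (Phase 1) compared to the enhanced intervention (Phase 2"). The second is a proportion with its own denominator: "the proportion of HPV-positive women in each arm who complete treatment". The efficacy hypothesis in Implementation framework is conditional in the same way: "A community-driven intervention will improve linkage to treatment among women who need treatment after an HPV-positive screening test compared to standard referral".

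A population denominator is defined in the endpoints section, but in the paragraph on reach: "The total number of women in each arm is the number of women 25–65 in each community as determined by census data".

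**The concern.** The linkage question is conditional: among women who test positive, how many are treated? A community-size offset makes the analysis unconditional: how many women are treated per member of the community? The second quantity moves with screening uptake and HPV positivity as well as with linkage. This trial expects uptake to differ between campaign and clinic, since that is its reach hypothesis.

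If the stated model were used for the second metric, a difference in uptake could be reported as a difference in linkage, and a real gain in linkage could be hidden or inflated. Whether size means all residents or women aged 25–65 does not alter this, because neither is the number of HPV-positive women.

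**Working it through.** **Inputs**, all from Sample size unless stated:
- Women available: "the total available population of women to be approximately 1000 per community of 5000".
- Expected screened in Phase 1: "510 women per community accessing testing through community health campaigns and 210 accessing screening through clinics".
- Resource ceilings: 4500 and 2000 women, that is 4500/6 = 750 and 2000/6 = 333 per community.
- Intracluster correlation for treatment: 0.11 (Statistical analysis).
- HPV positivity, linkage and Phase 2 reach are not given. The first two cancel below when equal in both groups. The third is varied.

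**Reproducing the plan's figures.** 6 × 510 = 3060 and 6 × 210 = 1260, the stated Phase 1 totals. Also 51% − 21% = 30 points, which matches the 30% difference used for power.

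**What the model estimates on community totals.** Treated = size × reach × positivity × linkage. With offset log(size), the rate ratio is

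(reach₁/reach₀) × (positivity₁/positivity₀) × (linkage₁/linkage₀).

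With offset log(number HPV-positive), the first two factors drop out and the linkage ratio remains.

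**Community versus clinic testing, the contrast in Statistical analysis.** With equal positivity and equal linkage, the size offset gives 0.51/0.21 = 2.43. The HPV-positive offset gives 1.00.

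A simulation agrees. It used a Poisson GEE with robust standard errors, 6 communities of 1000 women per group, intracluster correlation 0.11, assumed positivity 30% and linkage 50%, and 300 runs:
- Size offset: median ratio 2.40, p < 0.05 in 97% of runs.
- HPV-positive offset: median ratio 0.98, p < 0.05 in 13% of runs. The excess over 5% comes from robust standard errors with only 12 clusters and is a separate matter.

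**Phase 1 versus Phase 2 campaigns, the contrast in Primary and secondary endpoints.** Phase 1 reach is 510 per 1000, Phase 2 reach is assumed, and positivity is equal:

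| Phase 2 screened per 1000 | Ratio if linkage is equal | Ratio if the true linkage ratio is 1.5 |
|---|---|---|
| 300 | 300/510 = 0.59 | 0.88 |
| 400 | 400/510 = 0.78 | 1.18 |
| 510 | 510/510 = 1.00 | 1.50 |
| 600 | 600/510 = 1.18 | 1.76 |
| 750 | 750/510 = 1.47 | 2.21 |

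One way for reach to fall is prior screening. Study design and setting places Phase 2 in the former control communities, where 21% were expected to be screened in Phase 1. If none of those women return, 51% of the rest attend, and the denominator stays at all eligible women, reach is 0.79 × 0.51 = 0.40 and the ratio is 0.79 with no linkage difference. The abstract speaks instead of six additional communities, and there this mechanism would not apply.

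**Individual records of HPV-positive women.** With treated yes/no as outcome and offset log(size), reach does not enter. If all communities have the same size, the offset is a constant and goes into the intercept. If mean size among HPV-positive women differs between groups by a factor k, the ratio is divided by about k.

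**The case against.** The strongest reply is that the offset is right for what it was meant to do. The first efficacy metric is a count, and a log-link Poisson model with a community-size offset is a standard way to compare counts across communities. Implementation framework also has a population-impact hypothesis, for which treated women per community member is the quantity of interest. This stands. The offset is not wrong in itself, and it should be kept for those purposes.

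The GEE sentence before it covers number and proportion, with individual-level analysis, so the proportion may have been meant for a binary model among HPV-positive women. The Efficacy label may also be misplaced. Either is possible, but the text says neither. The only model form that it gives for efficacy carries the size offset. This is a matter of what the article states, not of detail left to an analysis plan.

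A reader might infer that the efficacy result will be inflated 2.43-fold. The documents do not support that. The figure needs community totals and the community versus clinic contrast, whereas the endpoints section compares two campaign-screened groups, to which the gap of 51% against 21% does not apply. Nor do they support a fixed bias of 0.79, which rests on the assumptions listed with it. If the model were fitted to individual HPV-positive women, the offset would do little harm while communities are of similar size, and the plan selected them to be so.

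**Conclusion.** The point holds in a limited form. The stated efficacy model matches the number treated and population impact. It does not estimate the proportion of HPV-positive women who complete treatment or test the linkage hypothesis, and no other efficacy model is given.

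On community totals, the distortion is 2.43-fold for the community versus clinic contrast, given the plan's own reach figures and equal positivity. For Phase 1 versus Phase 2 its size and direction are unknown, because Phase 2 reach is not stated. It is nil when reach and positivity are equal. The two sections also name different efficacy contrasts, which leaves open which of these cases applies.

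**What to change.** 1. For the proportion treated, restrict the analysis to HPV-positive women. Use a log-link modified Poisson or binomial GEE on treated yes/no, with no community-size offset. Alternatively, model community totals of treated women with offset log(number HPV-positive).
2. Keep the offset log(women aged 25–65) for reach and for treated women per eligible woman. Report the latter under its own name, as population impact, and say that size means women aged 25–65.
3. Reconcile the efficacy contrast between Primary and secondary endpoints (Phase 1 against Phase 2 campaigns) and Statistical analysis (community against clinic).

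The cost is a few sentences. No new data are needed, since test results and treatment are already recorded. By Trial status, Phase 2 was still being prepared, so the change can be made before its data exist.
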